#### Adherence and auditing

Participants can determine which components they use, in what combination and for how long over the 12-months intervention phase. Intervention providers will offer participants regular appointments (i.e., every one to two weeks) with low-threshold scheduling to enable regularity and structure. Although face-to-face appointments are preferred, also in terms if relationship building, intervention providers will offer online appointments as well where necessary. To facilitate face-to-face appointments, reimbursement of travel costs is offered.

Participating in a component can be paused or terminated within the time frame of the 12-months intervention phase. If participants state they would like to pause or terminate participation in one component, intervention providers will stress that the access to that component remains open within the 12-months period and encourage participants to contact intervention providers if their needs change and they would like to resume the component. Additionally, intervention providers will continuously encourage participation in the other two components where considered beneficial. If participants do not use any component for a certain time, research staff will regularly contact them to offer support via the intervention, potentially re-iterating the intervention components.

The intervention providers’ conduct and adherence to intervention manuals will be discussed in regular supervision meetings. Furthermore, every six months, there will be a fidelity assessment for each intervention component to review and, if necessary, further develop high fidelity in each component. The fidelity assessment will be conducted by an internal and an external reviewer based on predefined fidelity scales. Subsequent fidelity reports and emerging barriers will be discussed with the principal investigators and measures taken to improve intervention fidelity further if required.

### Assessments

Upon study entry, baseline assessment includes data collection on a variety of sociodemographic variables via a structured entry interview and an online questionnaire. These variables include age, gender, country of birth, citizenship(s), ethnicity, marital status, number of children, household income and debts, educational background, sick leave days, and history of homelessness. Additionally, participants will be asked questions in relation to their current unemployment status, employment history, and attempts and barriers to re-employment within the last 12 months. In relation to mental health, participants are asked questions in terms of mental health history (e.g., diagnoses, inpatient stays in a psychiatric or psychosomatic clinic), currently experienced symptoms and used treatment for mental health issues. The entry questionnaire also includes a screening for drug and alcohol abuse with the 4-item *CAGE-AID* instrument [71, 72].

After baseline assessment, further in-depth assessment takes place 12 months (t1; exit assessment) and 18 months (t2; follow-up assessment) after study entry, including structured interviews and online questionnaires. Additionally, every six months, participants are interviewed on their health service utilization as part of the cost effectiveness evaluation.

#### Primary outcome

The primary outcome is the proportion of participants who are in competitive employment in the primary labor market subject to social insurance contributions 12 months after study entry (yes vs. no). Competitive employment in the primary labor market refers to employment for which anyone can apply and which is not protected or accessible for individuals with disability status only. It will be assessed via self-report as part of the exit interview.

#### Secondary outcomes

Secondary outcomes encompass variables in relation to (re-)employment, health and well-being, social integration, help-seeking, and self-stigma. These variables will be assessed at t0, t1 and t2 by self-report, predominantly via online questionnaires, but also as part of structured interviews.

We will collect data on various variables related to (re-)employment. We will apply a one-item measure to ask participants about their *motivation to perform paid work* in the primary labor market [20], ranging from 1 (= *low*) to 3 (= *stron*g), with 4 (= *not applicable*,* as currently employed*) specifically for assessment at t1 and t2. Additionally, we will measure how confident participants feel in finding a job, namely job-search self-efficacy (JSSE). Variables regarding current employment status will be measured as self-report at t1 and t2 only (as the inclusion criteria at t0 preclude current employment). More specifically, participants will be asked in the exit and follow-up interview about employment they have started since entering the study or since the exit interview respectively. These questions encompass start and end date of potential employment, type of employment (e.g., part- or full-time employment, self-employment), working hours per week and average monthly net income. Finally, participants will also be asked about measures taken to obtain re-employment since the last assessment.

Furthermore, we will assess the following variables related to participants’ health and well-being in questionnaire format with established measurement scales: psychological distress, health-related quality of life, general health state, general well-being, somatic symptom burden, depressive symptoms, and symptoms of anxiety. Another set of measurement scales will assess participants’ social inclusion and social outcomes in relation to employment, housing situation, and social contact. Additionally, participants’ willingness to seek professional help for mental health issues and actual help-seeking behaviors in the last six months will be assessed. Finally, we will assess to which extent participants apply stigma toward mental health issues to themselves. As we will include participants who do not necessarily have a formally diagnosed mental illness, we change the introductory clause from the applied scale by Corrigan et al. [73] from “Because I have a mental illness, I …” to “Because I have mental health issues, I …”, for instance, “… will not recover or get better”.

Table 1 provides an overview of the employed measurement scales.

**Table 1 Tab1:** Overview of employed measurement scales for outcome variables

Variable	Scale	Scale source(s)	No. of items	Response range	Scale scores and interpretation	Reliability score(s)
Job-search self-efficacy	Job-Search Self-Efficacy Scale (JSSE)	[74]	6	1 = *not at all confident* to 5 = *great deal confident*	1–5 (mean score); higher score = higher level of job-search self-efficacy	α > 0.85 [22, 74, 75]
Psychological distress	Kessler’s Psychological Distress Scale (K6)	[58, 76]	6	0 = *none of the time* to 4 = *all of the time*	0–24 (sum score); higher score = higher level of psychological distress	α = 0.89-0.92 [58]
Health-related quality of life	EQ-5D-3 L	[77]	5	1 = *no problems* to 3 = *extreme problems*	The five responses are combined to present one of 243 possible health state profiles and evaluated based on country-specific value sets [78]	n/a
General health state	EQ-VAS	[77]	1	0 = *worst health* to 100 = *best health*	0-100; higher score = higher level of general health	n/a
General well-being	World Health Organization Well-Being Index (WHO-5)	[79, 80]	5	0 = *at no time* to 5 = *all the time*	0–25 (sum score); higher score = higher level of general well-being	α = 0.92 [80]
Somatic symptom burden	Somatic Symptom Scale (SSS-8)	[81, 82]	8	0 = *not at all* to 4 = *very much*	0–32 (sum score); higher score = more somatic symptoms	α = 0.81 [82]
Depressive symptoms	Patient Health Questionnaire (PHQ-9)	[83–85]	9	1 = *not at all* to 4 = *almost every day*	0–27 (sum score); higher score = more depressive symptoms	α = 0.88 [86]
Symptoms of anxiety	Generalized Anxiety Disorder Screener (GAD-7)	[87, 88]	7	0 = *not at all* to 3 = *nearly every day*	0–21 (sum score); higher score = more anxiety symptoms	α = 0.89 [88]
Social inclusion	Experiences of Social Inclusion Scale (ESIS)	[89]	10	1 = *strongly disagree* to 5 = *strongly agree*	10–50 (mean score); higher score = higher level of social inclusion	α = 0.89 [89]
Social outcomes	Social Outcomes Index (SIX)	[90]	4	Employment and living situation: 0 = [least preferable] to 2 = [most preferable Partnership/family and friends: 0 = [least preferable] to 1 = [most preferable]	0–6 (sum score); higher score = more preferable social outcomes	n/a
Help-seeking	General Help-Seeking Questionnaire (GHSQ) – adapted	[91, 92]	3	1 = *extremely unlikely* to 7 = *extremely likely*	3–21 (sum score); higher score = stronger intention to seek help from mental health professionals, general practitioners, or no one (reversed)	n/a (adapted)
Help-seeking	Actual Help-Seeking Questionnaire (AHSQ)	[92, 93]	2	0 = *no* 1 = *yes*	Acts of help seeking from mental health professionals evaluated individually	n/a
Self-stigma	Self-Stigma of Mental Illness Scale – Short Form (SSMIS-SF) – Subscale Apply	[73]	5	1 = *strongly disagree* to 9 = *strongly agree*	5–45 (sum score); higher score = higher degree of applying stigma to oneself	α = 0.74 [73]

As part of the t1 online questionnaire, we will ask IG participants to evaluate their intervention experience. We will first ask them to rate their overall satisfaction with the intervention on a visual analogue scale, ranging from 0 (= *lowest satisfaction*) to 100 (= *highest satisfaction*). Secondly, IG participants will be asked to rate their satisfaction with the intervention components in which they have participated in the intervention phase. For this rating, we adapt a questionnaire for client satisfaction with hospital stays (ZUF-8) [94] to fit our intervention components. Satisfaction with each intervention component will be evaluated with eight items; each item offering four response options. Thirdly, we will apply seven self-created items for each component to evaluate to which extent the components are considered helpful by participants for different aspects of their life (e.g., to change their situation, to find employment, to improve mental health). Each item will be rated in a 5-point Likert scale from 1 (= *strongly disagree*) to 5 (= *strongly agree*).

Additionally, we will assess health service utilization every six months with the *Client Socio-Demographic and Service Receipt Inventory* (CSSRI) [95] (German version: [96]) in order to evaluate the cost effectiveness of the 3for1-intervention program. The CSSRI will be completed via structured interviews, either as part of the interviews at t0, t1 and t2 or an additional interview six months after study entry.

In addition to the questionnaires and structured interviews, we will inquire data from job center records whether participants receive full basic income support benefits and for how many months they have received full benefits since study entry at 12, 18 and 24 months after study entry.

Finally, we will record the intensity of IG participants’ intervention utilization in our database: Intervention providers will record contact times (in minutes) with participants after every intervention session, including an overview of discussed topics. Based on these recorded contact times, we will calculate overall intervention utilization intensity as well as intervention component utilization intensity to explore whether more intensive utilization of the intervention and its components is associated with its effectiveness.

An overview of enrollment, intervention, and assessments across the different measurement points is given in Table 2.

**Table 2 Tab2:** Overview of enrollment, intervention, and assessments in the 3for1-project across measurement points

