= at least 21 months in basic income support within the preceding 24 months).*Hypothesis 5: *Twelve months after study entry (t1), participants in the intervention group will report significantly higher levels of job-search self-efficacy than participants in the control group.*Hypothesis 6: *Twelve months after study entry (t1), participants in the intervention group will report significantly more favorable outcomes on various psychosocial measures (i.e., psychological distress, health-related quality of life, general health state, somatic symptom burden, depressive symptoms, symptoms of anxiety, social integration, self-stigma) in comparison to participants in the control group.*Hypothesis 7: *Twelve months after study entry (t1), participants in the intervention group will report significantly higher intentions to and past acts of seeking professional help for mental health issues than participants in the control group.*Hypothesis 8: *Eighteen months after study entry (t2), participants in the intervention group will report significantly more favorable outcomes on the secondary outcomes mentioned in Hypotheses 5-7 than participants in the control group.*Hypothesis 9: *Of those job center clients that complete the screening measure for psychological distress, at least 30% will report experiencing at least moderate psychological distress indicated by a score of nine or greater on Kessler’s Psychological Distress Scale – K6 version [58].^1^

Furthermore, to evaluate the feasibility, implementation, and sustainability of the intervention components as regular service in job centers, we will conduct qualitative interviews with relevant stakeholders (e.g., job center executive board members, employment advisors, intervention providers, and intervention participants). Finally, we will evaluate the cost effectiveness of the 3for1-intervention program.

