### Sample size

We aim to recruit 500 participants, 250 participants per group. Sample size calculation is based on the primary outcome measure at t1 (i.e., employment status 12 months after study entry). Based on a previous longitudinal observational study with unemployed individuals with mental health issues [61], we assume a re-employment rate of 15% with TAU. We aim to achieve a re-employment rate of 30% in the IG. We conducted an a-priori power calculation for this expected intervention effect [62]: Applying a two-sided significance level of α = 0.05 and a statistical power of 0.90, we estimated that *n* = 161 participants in each group are required to show this effect. Based on previous research projects in this subject area, we anticipate a dropout rate of 35% between t0 and t1. To test the intervention effect for the primary outcome, we accordingly require an initial sample size of at least *n* = 248 participants per group at t0.

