#### Intervention components

##### Short-term psychotherapy

Participants can receive up to 10 sessions of short-term psychotherapy with a psychotherapist or psychologist with clinical training. Each session will last up to 50 min, which is equivalent to a regular psychotherapy session provided in the German outpatient health care system. In addition to a comprehensive anamnesis and clarifying the participants’ goals of the short-term psychotherapy, the initial sessions will focus on promoting motivation for change. The content of subsequent sessions may vary depending on the formulated goals and can include psychoeducation, developing a bio-psycho-social model of mental illness, resource work, developing a daily or weekly routine, or promoting problem-solving skills, self-efficacy, or social and emotional competencies. Promoting and maintaining motivation to change will be a topic throughout all sessions. Additionally, the indication for further treatment will be assessed. Accordingly, participants may receive a recommendation for further treatment and assistance in finding an outpatient or inpatient therapy place. In the last two sessions, the psychotherapy sessions are reviewed together and the need for booster sessions is assessed. Booster sessions could be indicated for the following goals: relapse prevention, maintenance of treatment gain, refresh learned skills, (re-)assessment of indication for further treatment, or support until continuing treatment starts. Up to three booster sessions can be offered on a case-by-case basis; indication will be discussed in supervision sessions. In general. they will be offered no sooner than two months after the last regular session.

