### Statistical methods

For the analysis of the primary outcome, logistic regression analysis will be applied. Logistic regression analysis enables the prediction of the binary outcome (in employment: yes vs. no) based on the binary group status (CG vs. IG), while controlling for relevant covariates such as the job center that the participant is registered with, the unemployment rate of the respective districts, duration of unemployment and of receiving basic income support, as well as baseline demographic variables which are significantly different in the two groups. The secondary outcomes will be analyzed with varied analysis methods based on the characteristics of the data: For the hypotheses which propose differences in binary outcomes (i.e., Hypotheses 3–4), logistic regression analysis will be applied; for hypotheses that predict difference in continuous outcomes (i.e., Hypotheses 2, 5–8), we will apply analyses of covariance to compare the two study groups. To estimate the prevalence of increased psychological distress in job center clients that complete the screening measure, we will conduct a frequency analysis (i.e., Hypothesis 9).

Additionally, we will analyze the cost-effectiveness of the intervention from two perspectives: We will address the intervention’s cost effectiveness in terms of benefits of employment for the social welfare state. More specifically, we will balance the costs for the intervention with the reduced costs for basic income support and related social welfare benefits. Furthermore, we will evaluate the intervention’s cost-effectiveness by relating the incremental total costs of illness, including the direct costs of health service utilization and the indirect costs of productivity loss, to the incremental gain in quality adjusted life years (QALYs) [97, 98].

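### At t1 the past-acts part of Hypothesis 7, as described, does not separate 3for1 psychotherapy from other professional help, and its yes/no items are assigned to ANCOVA

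*Protocol article*

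**What the plan says.** Hypothesis 7 (Objectives) predicts that at t1 the IG will report "higher intentions to and past acts of seeking professional help for mental health issues than participants in the control group". It therefore has two parts: intentions, measured by the GHSQ sum score, and past acts, measured by the AHSQ.

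For past acts, the Secondary outcomes section states that "actual help-seeking behaviors in the last six months will be assessed". Table 1 lists the AHSQ as two items coded 0 = no and 1 = yes, with the entry "Acts of help seeking from mental health professionals evaluated individually".

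The footnote to Table 2 places t1 at 12 months, immediately after the IG's intervention period ends, and t2 six months later. Within that period only the IG has access to the psychotherapy component: "Participants can receive up to 10 sessions of short-term psychotherapy with a psychotherapist or psychologist with clinical training". Up to three booster sessions may follow, case by case.

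On analysis, the Statistical methods section says that "for hypotheses that predict difference in continuous outcomes (i.e., Hypotheses 2, 5–8), we will apply analyses of covariance". It reserves logistic regression for binary outcomes and lists only Hypotheses 3 and 4 there.

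**The concern.** The six months covered by the AHSQ at t1 are months 6-12, wholly inside the 12 months of programme access. A psychotherapist or clinically trained psychologist is a mental health professional in the ordinary sense. An IG participant who saw the 3for1 therapist in that window has good reason to answer yes; a control participant has no such contact to report. The article describes no rule that keeps these contacts apart from help found elsewhere.

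A positive t1 result could then be reported as 3for1 making people more likely to seek professional help, when part or all of it may only record that the psychotherapy was delivered.

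Separately, the stated model does not match the stated outcome: two 0/1 items evaluated one by one are placed under a method that the same section reserves for continuous outcomes.

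**Working it through.** **The plan's own figure first.** The Sample size section gives the inputs: "Applying a two-sided significance level of α = 0.05 and a statistical power of 0.90"; "we assume a re-employment rate of 15% with TAU"; "We aim to achieve a re-employment rate of 30% in the IG". With pooled variance and no continuity correction, the mean rate is 0.225 and

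n = [1.960·√(2·0.225·0.775) + 1.282·√(0.15·0.85 + 0.30·0.70)]² / 0.15² = 160.8, so 161 per group.

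With 35% dropout, 161/0.65 = 247.7, so 248. Both stated figures reproduce, and neither is affected by this point. I use 161 per group as the evaluable number at t1.

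**The window.** Look-back at t1: months 12 − 6 = 6 to 12. Look-back at t2: months 18 − 6 = 12 to 18. Programme access: months 0 to 12. So the t1 window lies fully inside the access period and the t2 window lies after it.

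**Who can fall in the window.** The section on adherence offers appointments every one to two weeks. Ten sessions then end 9 to 18 weeks after the first, or 2.1 to 4.1 months (at 4.345 weeks per month). Someone who starts at entry and attends without a break finishes before month 6. Boosters generally come at least two months later, so from about month 4.1 to 6.1 at the earliest. Late starters, those who pause, and some booster users fall in the window.

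**Size.** The article gives neither of the two quantities needed, so both are assumptions:

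- p = share seeking professional help outside the programme, equal in both groups (no true effect);
- u = share of the IG seeing the 3for1 therapist in months 6-12, independent of p, with every such contact answered as yes.

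The control yes-rate is p. The IG yes-rate is p + (1 − p)·u. For example, p = 0.40 and u = 0.30 give 0.40 + 0.60·0.30 = 0.58 against 0.40.

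The chance of a significant result in favour of the IG, at two-sided 0.05 and for a single item, is

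Φ{ [d·√161 − 1.960·√(2·m·(1 − m))] / √(p₁(1 − p₁) + p₂(1 − p₂)) },

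where p₁ and p₂ are the control and IG yes-rates, d is their difference and m their mean. At u = 0 this is Φ(−1.960) = 2.5%, the IG-favouring half of the nominal 5%.

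| p | u = 0.05 | u = 0.10 | u = 0.20 | u = 0.30 | u = 0.50 | u giving 90% |
|---|---|---|---|---|---|---|
| 0.20 | 14% | 39% | 90% | 99.7% | ~100% | 0.20 |
| 0.30 | 10% | 26% | 74% | 97% | ~100% | 0.25 |
| 0.40 | 8% | 19% | 58% | 90% | ~100% | 0.30 |
| 0.50 | 7% | 14% | 44% | 78% | 99.7% | 0.35 |
| 0.60 | 6% | 11% | 32% | 62% | 98% | 0.42 |

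**The model.** In 2,000 simulated trials per setting, with no group effect, 161 per group and adjustment for the baseline item, a linear ANCOVA on the 0/1 outcome rejected in 4.9% and 4.8% of trials (baseline yes-rates 0.3 and 0.5). Logistic regression gave the same figures.

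**The case against.** The strongest reply is that the article never says programme contacts count. Table 1 gives the AHSQ one line, and item wording is the kind of detail a condensed article leaves to the full protocol. This stands: that 3for1 therapy is counted is an inference from the description, not a stated rule. What remains is that the hypothesis, window and measure, as described, do not prevent it.

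A reader might go further and infer that Hypothesis 7 is close to true by construction. The documents do not support that. GHSQ intentions are not scored by attending therapy. The psychotherapy is one of three optional components, used when the participant chooses, and early users can finish before month 6. At 5-10% exposure the artefact is modest.

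It can also be said that the data to untangle this exist: contact times are logged by component, and mental health treatment and service use are recorded separately at t1. That helps only partly. The log shows who saw the 3for1 therapist, not whether a yes referred to that contact, to outside help or to both.

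Hypothesis 8 already tests the same items at t2, free of the overlap. This stands and limits the point to t1.

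On the model, the Statistical methods section says that methods follow the characteristics of the data, and the Abstract names both logistic regression and ANCOVA for secondary outcomes. The assignment may be a slip in the list of hypotheses, but as written it is explicit. It would be wrong to infer that ANCOVA makes the test invalid; the simulation shows no inflation.

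A reader might also suspect that 3for1 sessions are costed twice through the CSSRI. Nothing in the article says they enter that inventory, so this is not part of the point.

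**Conclusion.** The point holds for the past-acts part of Hypothesis 7 at t1. Delivery of the programme's psychotherapy can be scored as an effect on help-seeking, because the look-back lies wholly inside the access period and the measure as described does not separate the two.

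The size cannot be fixed from the article. Under the assumptions above, the false signal ranges from small (about 6-39% at 5-10% exposure) to near certain (at least 90% once exposure reaches about 20-42%, depending on the outside rate). It rests on in-window uptake, on independence of programme and outside contact, and on participants answering yes for programme contacts.

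The assignment of the AHSQ items to ANCOVA, for Hypotheses 7 and 8 alike, is an internal contradiction of outcome type and method. It calls for correction but has no demonstrated effect on type I error.

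The reach is limited: one part of one secondary hypothesis at one time point, plus the model label at t1 and t2.

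**What to change.** 1. At t1, word the AHSQ items to exclude 3for1 providers, or ask about help inside and outside 3for1 as separate questions. Use the contact log only for a sensitivity analysis.
2. Base the conclusion on help-seeking behaviour on the t2 test already planned under Hypothesis 8. If the t1 items can no longer be reworded, report past acts at t1 descriptively.
3. Analyse each AHSQ item by logistic regression adjusted for its t0 value, and keep ANCOVA for the GHSQ score. Amend the list of hypotheses in the Statistical methods section accordingly.

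The cost is a small change of item wording at t1, a few lines of analysis text, and a behaviour conclusion that rests on somewhat fewer respondents at t2.
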